### 13.4 Handling of adverse event

In the event of an adverse event, the investigator decides whether to terminate the trial based on the subject's condition; in the event of a serious adverse event, the investigator must immediately conduct the correct treatment or rescue treatment to protect the subject's safety.

The main measures to be taken in the event of an adverse event include:

- 1) observation only;
- 2) dosage adjustment of the investigational drug or dose interruption;
- 3) withdrawal of the investigational drug;
- 4) treatment of concomitant medications;
- 5) non-pharmacological therapies;
- 6) hospitalization or prolongation of hospitalization.

### 13.5 Recording of adverse event

Serious adverse event occurring after acquirement of Informed Consent Form and before the end of the trial; all adverse events need to be recorded in the corresponding section of the CRF after acquirement of Informed Consent Form until subject out, regardless of whether the adverse event is related to the investigational drug, unless the subject withdraws the informed consent and follow-up visit cannot be performed.

All adverse events should be recorded in concise medical terms include: ① a description of adverse event and all associated symptoms; ② the time of occurrence and the duration of adverse event; ③ the severity of the adverse event; ④ the examinations and treatments performed due to the adverse event; ⑤ the final outcome of adverse event; ⑥ judge whether the adverse event was related to the investigational drug (if it could be judged).

### **13.6 Reporting of serious adverse event**

If all serious adverse events are judged as serious adverse events, the investigator should report to the sponsor and the drug regulatory department within 24 hours, regardless of whether the adverse events are related to the investigational drug or trial operations. The sponsor has responsibility for reporting the serious adverse event to the Department of Drug Administration and other clinical trial centers for the same drug in accordance with the regulations. Unless other requirement from the local regulatory authority and other documentation from the Ethics Committee, the investigator should also report the serious adverse event to the Ethics Committee that approved the protocol in accordance with the regulations.

The investigator fills in the Serious Adverse Event Report Form with a detailed description of the course of adverse event, the diagnosis, the treatment given, and the possible relationship to the drug. Follow-up report should be completed and reported to all parties according to the initial reporting procedures if the diagnosis is unclear or changed after it has been reported, or there is an important change in the subject's condition (e.g., the adverse event progresses to death from prolongation of hospitalization).

Serious adverse events should be sent by the investigator to the sponsor or the supervisor by fax:

Fax number:

Contact for the sponsor:

Phone number:

The sponsor should report the serious adverse event to the following department within 24 hours after receiving the Serious Adverse Event Report Form from the investigator:

China Food and Drug Administration, Department of Research Supervision:

Shanghai Food and Drug Administration, Registry:

When the investigator and sponsor report serious adverse event to related departments, the

relevant correspondence records should be stored, such as fax-sending reports, handover documentation, telephone records, etc.

### **13.7 Trail and follow-up visit of adverse event**

All adverse events should be followed up with detailed documentation of handling process and outcome, until they are appropriately resolved or stable. Any laboratory test results that are still abnormal at the end of the trial should be followed up by the investigator until they return to be normal or are clinically stable. According to the severity of adverse event, the distance of the subjects' residence from the hospital, and the medical specialty of the trial center, various forms of follow-up visit can be selected, such as inpatient, outpatient, home visit, telephone, and communication. The outcomes of all adverse events should be recorded in the CRF timely, and if the adverse event has not recovered by the end of the trial, the investigator should continue to follow the subject and record the relevant results in the medical record.

All serious adverse events should be followed up until the events are fully resolved; and at least one follow-up or summary report should be provided to detailed describe the treatment given to the subject, the outcome of subject's condition, the final diagnosis, and the relationship between final diagnosis and investigational drug, since the onset of the serious adverse events. The summary report of the serious adverse events should be reported to the sponsor and the Ethics Committee in accordance with the initial report procedures, and should be also reported to the Department of Drug Administration by the sponsor.

### **13.8 Expected adverse reaction and handling**

#### **13.8.1 Risk assessment of the trial**

Based on the clinical trial data from systemic administration of AAV drug, the risk of serious adverse events associated with AAV drugs includes hepatotoxicity (elevated liver enzymes, liver failure, etc.), thrombocytopenia, hemolysis, anemia, acute kidney injury, and neurotoxicity found on MRI. The local administration of AAV drug in the clinical trial such as ophthalmic trial gives rise to few systemic toxicity, mainly local inflammation at the site of administration and systemic reactions due to hormone administration at the same time.

Based on the data from drug administration by injected into inner ear of patients with profound

deafness in clinical trials, adverse reactions may be associated with AAV drugs, injection procedures, concomitant corticosteroids or a combination of these procedures and products. The most common adverse reactions (>5%) in the ear include mild hearing loss, dizziness, lightheadedness, nausea, and vestibular dysfunction, etc. Other adverse reactions with an incidence of less than 5% include otalgia, ear bleeding, unilateral deafness, tinnitus, taste change due to the injury of chorda tympani nerve, otitis media, perilymphatic fistula, reparative granuloma and tympanic membrane perforation, facial palsy, inner ear infection and meningitis, and sinusitis, etc. Systemic adverse events include hepatic impairment (elevation of ALT, AST, etc.), fatigue, food allergies, seasonal allergies, atopic dermatitis, urticaria, etc. These are systemic events that may be caused by systemic administration of corticosteroids and anesthetic reactions.

In summary, this clinical trial may be exposed to risks caused by the above-mentioned adverse reactions and risk control will be performed during the clinical trial to ensure the safety of the subjects.

#### 13.8.2 Treatment Precautions

In accordance with the regulations of NMPA's new GCP, patients who are ready to participate in the trial will be screened strictly according to the inclusion and exclusion criteria, avoiding to include patients who do not meet the criteria in the trial. To guarantee the safety of subjects, risk control will be carried out during the trial and is planned as follows:

- (1) Multiple follow-up visits will be performed before dosing, during the treatment and thereafter, including subject's general condition, clinical signs and symptoms, any adverse events during discharge, medical physical examination, observation of injection site reactions and other adverse events, and otologic examinations. Otologic examinations include ear inflammation, ear infection, ear bleeding, pure tone test, speech recognition, ABR, DPOAE, vestibular assessment, etc. Laboratory tests include blood, urine, function of liver and kidney, blood electrolytes, coagulation. Monitor the occurrence of adverse events specially. The above contents include the safety indicators for RRG-003, aiming to control possible adverse drug reactions and risk factors during the trial.
- (2) Monitor and control possible adverse drug reactions and risk factors during the trial by signs and symptoms, laboratory tests, and otologic imaging; and give advice on handling.
- (3) The subject can withdraw from the trial at any time during any phase of the trial.

(4) The safety and efficacy data from this trial are regularly analyzed by the principal investigators and/or statisticians, who decide whether the trial should be continued.

(5) If the subject experiences an adverse event related to the investigational drug during the trial, the following principles need to be followed for handling of adverse event.

If an accident occurs during inner ear surgery, terminate injection promptly. And medical treatment should be conducted by the investigator;

Adverse events that do not meet the DLT during the observation of DLT are not treated generally;

After completion of DLT observation, adverse events should be handled actively;

Once adverse event happens in the subject, the investigator is responsible for making relevant medical decisions based on clinical practice to ensure that the subject is treated appropriately and the handling of AE should be documented.

(6) Risk of infection after inner ear drug administration

Nurse the subject carefully during the perioperative period of inner ear surgery; prevent infection with antibiotics and glucocorticoids after surgery. Contact the investigator promptly if subject fails to comply with medical advice or an accident occurs.

(7) Other toxic reactions: Symptomatic treatment is available. If blood tests and urine tests are abnormal, collect and detect samples again within 24 hours; and the corresponding treatment or therapy should be performed according to the test results.

(8) Risks associated with dexamethasone via intravenous injection:

Dexamethasone can reduce postoperative inflammation and decrease the immune response to AAV drugs, and is often used before and after ear surgery.

Common side effects of dexamethasone include increased appetite, stomach upset, nervousness, or restlessness. Less common but serious side effects include decreased or blurred vision, fluid retention, weight gain, increased blood sugar level, frequent urination, thirst, mood swings, confusion, and rash or urticaria. Other rare side effects include darkening or brightening of the skin, dizziness, facial flushing, hiccups, and increased sweating.

Dexamethasone may reduce resistance to the infection, which may lead to a sore throat, fever, sneezing or coughing.

Once side effects occur, discontinue dexamethasone immediately.

(9) General anesthesia:

Serious but very rare adverse events (negative side effects) associated with any types of anesthesia/surgery include seizures, coma, and death.

Rare but serious complications associated with general anesthesia include cardiac arrhythmias, increased or decreased blood pressure, transient high fever, rare reactions to drugs used in anesthesia, and airway obstruction.

The risk associated with a small amount of local anesthesia is low. Anesthetic injection is accompanied with a small risk of penetration of the eye or optic nerve, and the possibility of hemorrhage, which need to be treated if necessary.

(10) Risks associated with surgery:

1. Injury to ear ossicles such as injury to stapes, resulting in the dislocation of stapes; or even injury to oval window, leading to perilymphatic fistula.

2. Injury to jugular bulb, causing hemorrhage. In the event of hemorrhage, the ear canal should be filled with pressure to stop bleeding.

3. Facial paralysis, is usually caused by injury to the facial nerve or excessive strain on the chorda tympani nerve. If facial paralysis occurs, analyze the cause and perform facial nerve decompression surgery timely if necessary.

4. Labyrinthitis: nurse surgical cavity carefully after surgery; and use antibiotics and glucocorticoids that can cross the blood-brain barrier to prevent the spread of inflammation; persist with follow-up visit.

5. Post-operative infection, short or long-term ear discharge, perichondritis. Strictly grasp the surgical indications and contraindications before surgery and pay attention to aseptic operation during surgery. Dressing should be changed after surgery, and granulation in the surgical cavity should be treated in time to protect the new epithelium. Pay attention to drainage and removal of secretions.

6. Tinnitus.

7. Cerebrospinal fluid leak. Promptly repair it with mastoid cortex and temporalis fascia.

8. Taste change, usually caused by injury of chorda tympani nerve.

(11) Thrombocytopenia:

1. Hemostasis: in the event of hemorrhage, stop bleeding via antihemorrhagic, prevent internal bleeding, and then identify the cause.

2. Hormone therapy: In the event of mucous membrane or more extensive skin bleeding, treat the subject with adrenocortical hormone to control the condition and reduce the damage to the body. Use estrogen for a short time in an acute condition.

3. Blood transfusion: When a platelet count is less than  $30 \times 10^9/L$  with continuous bleeding, platelet transfusion should be performed in time to stop bleeding as soon as possible.

In conclusion, according to the risk control plan, the possible risks of RRG-003 during the trial are controlled, and suggestions are made for the treatment of possible adverse reactions, ensuring participants take drugs reasonably and safely.

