| Otitis externa                                 | Oral intervention indicated

(e.g., antibiotic, antifungal, or

antiviral)                                          | IV antibiotic, antifungal, or

antiviral intervention

indicated; invasive

intervention indicated                                                                                    |
| Otitis media                                   | Localized; oral intervention

indicated (e.g., antibiotic,

antifungal, or antiviral)                               | IV antibiotic, antifungal, or

antiviral intervention

indicated; invasive

intervention indicated                                                                                    |

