### Postoperative care

6. Before waking up from general anesthesia, the patient was lay down on the pillow with the head turned to one side. After waking up, take the supine position and do not press the injected ear. Do not move the head excessively. According to the doctor's advice, give ECG monitoring (closely observe the changes of vital signs), oxygen inhalation, and blood oxygen saturation monitoring (SPO2 above 90%).
7. Intravenous injection of third-generation cephalosporin antibiotics start on the day of post-operation lasts for 5 days to prevent infection. Glucocorticoids could be used appropriately if accompanied by obvious acute dizziness.
8. Observation and nursing of whole brain syndrome. Closely observe the changes of vital signs, and continuously monitor the patient's consciousness, pupil, blood pressure, pulse, and respiration after waking up from general anesthesia. If the patient vomits, attention should be paid to distinguish whether it is a reaction after general anesthesia or an intracranial complication. If the blood pressure rises progressively, the pulse is slow and powerful, the breathing is deep and fast, the body temperature rises, and headaches are accompanied by changes in consciousness and pupils, one should be alert to the occurrence of intracranial complications and immediately report to the doctor for treatment.
9. Observation and nursing of local wound conditions. Observe whether the ear dressing oozed blood, keep the external ear canal clean, and prevent sewage from entering the ear. Do not blow the nose hard, and wipe it off gently to prevent backflow to the middle ear causing infection.
10. Observation and nursing of facial nerve function. Pay attention to whether there is injury of the facial nerve and chorda tympani nerve, focusing on observing whether there are facial paralysis manifestations such as crooked mouth corners, inability to close eyelid, reduction or disappearance of forehead lines, and taste alteration. Glucocorticoids, neurotrophins and physiotherapy should be applied once facial paralysis occurs.

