#### 18.3 Any AE occurred during the trial can be effectively managed and followed up

If any adverse event occurs during the trial, the investigator can decide whether to terminate the trial based on the condition. Once an adverse event occurs, the investigator will immediately implement appropriate treatment or rescue treatment to protect the safety of the subject.

All adverse events will be followed up until they are properly resolved or stabilized. According to the severity of adverse event, the distance of the subjects' residence and the hospital, and the medical specialty of the trial center, hospitalization, outpatient visit, home visit, telephone, and communication can be selected.

RRG-003 meets the requirement of IIT clinical trial in terms of quality standard, animal pharmacodynamics and safety.

This protocol follows the ethical principles of medical research involving human subjects outlined in the Declaration of Helsinki, is consistent with the ethical principles of medical research involving human subjects, and benefits all subjects as far as possible.

Although there is no guarantee that the result of this trial will be as expected, it is possible that the condition of subjects participating in the trial will improve. At the same time, all investigational drugs and related examinations required by the protocol are free.

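### Protocol v5.0 gives conflicting instructions on treating drug-related adverse events below DLT level during the 42-day DLT window

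*Supplement*

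**What the plan says.** All references are to protocol v5.0.

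- **Section 13.8.2, item (5).** Its scope is set by the opening condition: "If the subject experiences an adverse event related to the investigational drug during the trial". Within that scope, "Adverse events that do not meet the DLT during the observation of DLT are not treated generally". The next line reads: "After completion of DLT observation, adverse events should be handled actively". The item closes with: "Once adverse event happens in the subject, the investigator is responsible for making relevant medical decisions based on clinical practice", so that the child is treated appropriately and the handling is documented.
- **Section 13.8.2, item (7).** For abnormal blood or urine results, samples are retaken within 24 hours and "the corresponding treatment or therapy should be performed according to the test results".
- **Section 13.8.2, item (11).** For thrombocytopenia it directs hormone therapy when there is mucous membrane or more extensive skin bleeding, without reference to grade or to the DLT window.
- **Section 18.3.** "Once an adverse event occurs, the investigator will immediately implement appropriate treatment or rescue treatment to protect the safety of the subject".
- **Section 4.3, criterion 9.** During the six-week evaluation period, a need for other treatments leads to withdrawal.
- **Section 3.1.** DLT is hematologic toxicity of grade 4 or more, non-hematologic toxicity of grade 3 or more, or ear toxicity of grade 2 or 3, within 42 days.
- **Section 11.** DLT at week 6 is the primary indicator.

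**The concern.** Item (5) sets a default for the DLT window that differs from the default afterwards: leave sub-DLT events alone first, handle them actively later. Section 18.3 knows no such window. An investigator facing a drug-related event below DLT level can therefore find support in the protocol for holding back, for treating at once, or for treating and withdrawing the child.

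Two things are at stake. The participants are children aged 1-18, and instructions on their care should not contradict each other. And the same 42 days define the primary indicator. If care in that window depends on which passage was followed, the DLT record no longer comes from one stated regime of care, and nobody reading it can tell which regime applied.

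**Working it through.** The plan gives no figure on this point, so there is none to reproduce. The check is a comparison of texts, followed by a small calculation of how much the escalation rule can depend on one event.

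**Step 1. Which events are affected.** Item (5) covers drug-related events that are not DLTs. Taking the complement of the definition in Section 3.1:

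- hematologic: DLT from grade 4, so grades 1-3 are affected;
- non-hematologic, outside the ear: DLT from grade 3, so grades 1-2 are affected;
- ear: DLT at grades 2 and 3, so only grade 1 is affected.

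**Step 2. One event under each passage.** Take a drug-related, non-ear, non-hematologic grade 2 event on day 10 (a constructed example).

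- Item (5), second rule: generally not treated until the window closes, 42 − 10 = 32 days later.
- Item (5), last sentence: the investigator decides on clinical practice. The text does not say whether this overrides the second rule.
- Section 18.3: appropriate treatment at once.
- Criterion 9: if the event is read as requiring other treatment, withdrawal. Section 5 counts as effective only a case observed for at least six weeks, so this reading can also affect who is evaluable.

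Items (7) and (11) add a conflict for laboratory events. A drug-related hematologic event of grade 1-3 is below DLT level and so falls under the general no-treatment rule, yet these items direct treatment without any exception for the window.

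**Step 3. Link to the primary indicator.** DLT depends on the grade reached by day 42. It is possible that an untreated sub-DLT event progresses to the threshold and a treated one does not. That is inference; no passage states it.

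**Step 4. How much one event weighs.** At 30 µL, the first child's DLT status alone decides whether the next child may enter 50 µL (Section 3). At 50 µL, expansion needs no DLT in 3-5 children or at most one in 6. One event is 1/3 = 33 percentage points of the observed rate among three children and 1/6 = 17 points among six. These figures describe any single event in groups of this size; they do not measure the effect of item (5).

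As an illustration, simplify the 50 µL rule to: pass with 0 of 3, or with 1 of 3 followed by 0 of 3 more. With an assumed true DLT probability p,

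P(pass) = (1−p)³ + 3p(1−p)² × (1−p)³

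P(at least one DLT in 3) = 1 − (1−p)³

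| p (assumed) | P(pass) | P(at least one in 3) |
|---|---|---|
| 0.05 | 0.973 | 0.143 |
| 0.10 | 0.906 | 0.271 |
| 0.20 | 0.709 | 0.488 |
| 0.30 | 0.494 | 0.657 |
| 0.40 | 0.309 | 0.784 |

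For p = 0.10: 0.729 + 0.243 × 0.729 = 0.906. For p = 0.20: 0.512 + 0.384 × 0.512 = 0.709. If handling moved the true rate from 0.10 to 0.20, the chance of passing would fall from about 91% to about 71%. The documents give no ground for that shift or any other; the table shows only that the rule is sensitive to the rate.

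**The case against.** The strongest reply is that the texts can be read together. Item (5) says *generally*, and its last sentence can serve as the exception. Section 18.3 speaks of *appropriate* treatment, and Section 13.4 lists observation only as the first measure for an adverse event, so watching a minor event may itself count as appropriate handling. This stands in part. A reader might infer that item (5) leaves children untreated in a way that other passages forbid; given these softening words, the documents do not support that much. But *generally* names no exceptions, and the contrast with active handling afterwards shows that a separate default for the window was meant. Section 18.3 does not acknowledge it.

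Three further objections hold:

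- **Facial paralysis.** The postoperative care text says "Glucocorticoids, neurotrophins and physiotherapy should be applied once facial paralysis occurs". Item (10) of Section 13.8.2 places facial paralysis among surgical risks, usually from nerve injury or strain, so it mostly falls outside item (5). It conflicts only if attributed to the drug.
- **Ear grades.** It is tempting to call treating and grading circular, because otitis externa of grade 2, for example, is defined by "Oral intervention indicated". The criterion is that intervention is indicated, not that it is given, so withholding treatment does not change that grade. Ear grade 2 is already a DLT and so lies outside the no-treatment sentence.
- **Data capture.** Section 13.5 already requires severity, time of occurrence, duration and treatments performed to be recorded for every adverse event. Only the treatment date is not named.

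**Conclusion.** The point holds as a conflict of instructions in the current protocol. Section 13.8.2(5) and Section 18.3 set different defaults for the same drug-related, sub-DLT event, and the last sentence of item (5), items (7) and (11), and criterion 9 do not settle which governs.

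The reach is limited to children who actually have such an event within the 42 days, in the grades listed in step 1. It is not every participant for the whole window.

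A reader might go on to infer that the DLT count is distorted. That goes beyond the documents: they give no rate at which sub-DLT events occur, nothing on whether they progress untreated, and no sign of which passage sites would follow. Uneven handling could affect the count, in an unknown direction and by an unknown amount. The text should still be repaired, because it concerns the care of children in the window that defines the primary indicator, and in groups this small one event can decide escalation.

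**What to change.** Reconcile Section 13.8.2(5) with Section 18.3, with items (7) and (11) of Section 13.8.2, and with criterion 9 of Section 4.3, so that one instruction governs adverse-event handling during the DLT window and applies alike to all participants. It should say how the investigator's judgement in the last sentence of item (5) relates to the general rule, and whether treatment given in the window has any bearing on withdrawal under criterion 9. Which clinical rule to adopt is for the sponsor and investigators.

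For the data, add the date of any treatment to what Section 13.5 already collects, and show treatment and date beside the worst grade whenever a DLT decision is made. Each decision can then be read with the care actually given.

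The cost is one reconciled passage with matching edits where it is echoed, and one CRF field. No extra patients or visits are needed.
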